### 2.4. ENT Screening

At the start of the study, all children will undergo an Ear Nose Throat (ENT) examination to evaluate anatomy and functionality of the orofacial structures (Table 1). This initial assessment is crucial for understanding the baseline characteristics of the participants and determining any potential abnormalities that may impact the study outcomes. Table 1 provides an overview of the components of the ENT examination.

### 2.5. Demographic and Medical Questionnaire

At the start of the study, parents of children will be asked to fill out a questionnaire concerning medical (e.g., previous OSA treatments, timing of adenotonsillectomy) and demographic (e.g., sex, age, weight) information of their child. By recording these variables, the study aims to better understand variability in treatment outcomes and identify subgroups that may benefit most from the intervention.

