## 2. Materials and Methods

### 2.1. Participants

#### 2.1.1. Non-Syndromic Children

Children with OSA will be recruited via the Pediatric Sleep Center, the Otorhinolaryngology and the Pneumology department of Ghent University Hospital. They will be selected to participate in the study based on the inclusion criteria: aged between 4 and 18 years, diagnosed with OSA confirmed by an oAHI > 1 on polysomnography. The lower age limit is chosen because a certain level of maturity is required before a child is capable to understand and perform OMT exercises [10]. Exclusion criteria are: history of OMT, orthodontic treatment in progress, other OSA treatments in progress, orofacial congenital deformities, nasal congestion, intellectual disability and obesity (>2 SD above P50). Both children with and without previous surgical removal of adenoids and/or tonsils will be included. Inclusion and exclusion criteria will be assessed through a questionnaire and an ENT examination.

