### 2.2. Sample Size

Based on a study of Villa, Evangelisti, Martella, Barreto and Del Pozzo [32], a sample size of *n* = 23 was calculated for the pretest–posttest study in non-syndromic children (G*Power, McNemar test, 2-sided). Calculation was based on the outcome ‘oral breathing’ with an α level of 0.005 (to account for multiple testing), a power of 0.80, and a decrease of 66.7% (12/18) in the proportion of children exhibiting oral breathing post-intervention. Taking into account a dropout rate of 15%, *n* = 27 will be the target in the study. For the pretest–posttest study in children with Down syndrome, sample size calculation is not yet possible given the innovative nature of this objective.

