### 2.3. Design

Two separate pretest–posttest studies will be conducted to determine the effects of OMT in the management of pediatric OSA in non-syndromic children (pretest–posttest study 1) and children with Down syndrome (pretest–posttest study 2). Intervention will consist of a 10-week OMT in non-syndromic children and a 20-week OMT in children with Down syndrome [35]. Both studies include 2 measurement moments: (1) at the start of the study (baseline), and (2) after the therapy period. All measurement moments consist of an evaluation of orofacial myofunctional, sleep, and quality of life outcomes. To avoid observer bias, all assessments will be performed blindly, so assessors will be blinded to group allocation and study phase.

To reduce the number of therapy sessions and investigations in these children, no sham therapy will be used. Because of the complexity of OSA and the variability in patients within the objective, it is chosen not to compare the results against a control group but to look at performance at an individual level.

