### 2.9. Statistical Analysis

For the analysis of intervention effects, a paired sample t test (continuous, parametric), Wilcoxon signed rank test (continuous, nonparametric), or McNemar test (nominal) will be used. Intraclass correlation coefficient models and Cohen’s kappa will be used to determine inter- and intrarater reliability.

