Both objective measures (e.g., polysomnography, tongue strength) and subjective/patient-reported outcomes (e.g., sleep quality questionnaires) will be collected to assess the potential of OMT in treating pediatric OSA. Unlike previous pediatric studies, changes in OSA severity will not be limited to alterations in AHI alone. While the AHI is often used as the holy grail when it comes to grading OSA severity, it has become clear that the AHI has several inherent shortcomings and therefore it does not capture the full complexity of sleep-disordered breathing [32]. By evaluating a wide range of objective polysomnographic outcomes—including oxygen desaturation indexes, arousal indexes, sleep efficiency, and sleep architecture metrics—in addition to AHI, this study will provide a more comprehensive understanding of how OMT impacts OSA. In addition to objective measurements, validated questionnaires will be used to assess the impact of OSA on the child’s daily functioning and overall well-being. To the best of our knowledge, no previous studies have examined the effect of OMT as primary treatment for pediatric OSA. However, it can be assumed that replacing invasive surgical treatments, such as AT, with functional therapy would greatly benefit the child by eliminating the risk of surgical complications and exposure to anesthesia. Non-syndromic children without a history of AT will therefore also be included in the study. Another strength of this study is the implementation of a detailed therapy plan in which all therapeutic goals and exercises are described. This contrasts with previous research, where patients followed varying therapy programs with limited information on their content. Providing a comprehensive overview of the exercises used enhances reproducibility and facilitates both future research and clinical application. As for the design of the study, the efficacy of OMT will be evaluated in both non-syndromic children and children with Down syndrome by the use of a pretest–posttest design. While it is acknowledged that randomized controlled trials are often considered the gold standard from a methodological perspective, it is chosen not to adopt this design in the current study. There are both ethical and practical considerations that informed this decision. Ethically, exposing children to sham therapy or additional investigations without therapeutic benefit was deemed inappropriate, particularly given the vulnerability of the study population. Furthermore, given the complex and heterogeneous nature of OSA, especially in pediatric patients, a within-subject design allows us to better capture meaningful changes by comparing each child’s post-intervention outcomes to their own baseline performance. By not dividing the sample into treatment and control groups, we ensure that a larger proportion of children receive the actual therapeutic intervention. This is particularly valuable in a pediatric context, where reducing the burden of treatment and maximizing potential benefit is paramount. However, it must be acknowledged that the absence of a control group limits the inferential strength of the study. Without randomization, the design is susceptible to potential biases, including placebo effects and the influence of unmeasured confounders. Additionally, no formal sample size calculation could be performed for the Down syndrome group due to the exploratory and novel nature of this objective, which presents another methodological limitation. These factors should be considered when interpreting future findings, and they underscore the need for follow-up studies using more robust designs to confirm the efficacy of OMT in this population.

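### With one arm and two measurements, the baseline variables can show which children change most, not which benefit most from OMT, so the tentative subgroup aim in section 2.5 should be reworded

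*Protocol article*

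**What the plan says.** Section 2.5 (Demographic and Medical Questionnaire) explains why parents are asked for background data. Its examples are medical ("previous OSA treatments, timing of adenotonsillectomy") and demographic (sex, age, weight). It gives two purposes: to understand variability in outcomes, and to "identify subgroups that may benefit most from the intervention".

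Section 2.3 (Design) fixes the structure in which this would be done. There is no comparator: "it is chosen not to compare the results against a control group but to look at performance at an individual level". There are two time points: "Both studies include 2 measurement moments: (1) at the start of the study (baseline), and (2) after the therapy period". No untreated waiting period or repeated baseline is described.

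Section 2.9 (Statistical Analysis) lists within-child tests for intervention effects: "a paired sample t test (continuous, parametric), Wilcoxon signed rank test (continuous, nonparametric), or McNemar test (nominal) will be used".

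Section 3 (Discussion and Conclusions) acknowledges that "the absence of a control group limits the inferential strength of the study" and mentions placebo effects and unmeasured confounders. It does not mention subgroups, natural course or regression to the mean. The same section argues that the within-subject design captures meaningful change better.

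**The concern.** To say that a subgroup benefits more from an intervention is to say that the intervention makes a larger difference there than elsewhere. That is a statement about effect modification, and it needs an estimate of what would have happened without the intervention in each subgroup. This design observes only the total change.

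If a baseline variable is related to untreated change, to regression to the mean after selection on an oAHI threshold, or to parents' reporting, it will appear to identify responders even if OMT works equally in everyone or in no one. The opposite can also happen: a true responder subgroup is hidden if the other subgroup improves by itself.

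A prognostic association could then be read as guidance on which children to treat with OMT. No later choice of analysis can repair this, because the missing information is not collected. It is therefore not a detail that could be settled in an analysis plan that is not shown.

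**Working it through.** **Inputs from the protocol article**
- One group, two measurements (section 2.3).
- Paired tests only for intervention effects (section 2.9).
- Non-syndromic study: n = 23, raised to a target of 27 for 15% dropout, with alpha 0.005 two-sided (section 2.2). No sample size is calculated for the Down syndrome study.
- Entry criterion in the non-syndromic study: "diagnosed with OSA confirmed by an oAHI > 1 on polysomnography" (section 2.1.1). The Down syndrome study uses the same oAHI threshold (section 2.1.2).

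The article gives no figure for subgroup differences, so there is none to reproduce. The target agrees with its own inputs to within rounding: 23 / 0.85 = 27.06, and 27 × 0.85 = 22.95. The point does not depend on the sample size.

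**Step 1: what is identified.** For subgroup g, expected change = OMT effect(g) + untreated change(g). Between subgroups A and B:

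difference in change = [OMT effect(A) − OMT effect(B)] + [untreated change(A) − untreated change(B)].

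The design gives the left side. The aim concerns the first bracket. The two agree only if untreated change is equal in the subgroups, which the article neither assumes nor supports.

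**Step 2: simulated check.** 12 versus 11 children, SD of change 1, two-sample t test at 0.05, 20,000 runs. All effects are assumed; negative values mean improvement.

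| OMT effect A / B | Untreated change A / B | Mean change A / B | Significant difference |
|---|---|---|---|
| 0 / 0 | −1 / 0 | −1.00 / 0.00 | 63% |
| −1 / 0 | 0 / 0 | −1.00 / 0.00 | 63% |
| −0.5 / −0.5 | −1 / 0 | −1.50 / −0.50 | 63% |
| −1 / 0 | 0 / −1 | −1.00 / −1.00 | 5% |

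Rows 1 and 2 have the same data distribution and opposite meanings. In row 3 the OMT effect is equal and a subgroup difference still appears. In row 4 a true responder subgroup is missed.

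**Step 3: regression to the mean alone.** Zero treatment effect, with assumed SD of log oAHI 0.8 and test-retest correlation 0.6 to 0.8. Among children entering with oAHI above 1, about 15% to 21% of a mild subgroup (assumed mean log oAHI 0.3) fall to 1 or below at retest. In a more severe subgroup (assumed mean 1.5) about 2% do.

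**Step 4: illustrative frequency of a spurious difference.** Two-sample t test, no difference in OMT effect, and untreated change differing by d SD (assumed). Noncentrality = d / √(1/n₁ + 1/n₂). For 14/13, √(1/14 + 1/13) = 0.385, so d = 0.3, 0.5 and 0.8 give 0.78, 1.30 and 2.08 on 25 degrees of freedom. For 12/11 the divisor is 0.417, on 21 degrees of freedom.

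| Split | Alpha | d = 0.3 | d = 0.5 | d = 0.8 |
|---|---|---|---|---|
| 14/13 | 0.05 | 12% | 24% | 51% |
| 14/13 | 0.005 | 2% | 5% | 19% |
| 12/11 | 0.05 | 11% | 21% | 45% |
| 12/11 | 0.005 | 2% | 4% | 14% |

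**Step 5: precision.** With 23 completers split 12/11, 80% power needs a subgroup difference of about 1.2 SD at alpha 0.05, or 1.7 SD at 0.005. Even as description, the estimates will be imprecise.

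**The case against.** The strongest reply is that the article does not promise a subgroup analysis. The words are half of one sentence justifying a questionnaire, hedged with *may*, and no subgroup hypothesis, responder definition or subgroup test is given. The objectives in the Abstract and in sections 2.3 and 2.6 concern overall effects of OMT. The Discussion already discloses the missing control group, asks that it be considered when interpreting findings, and calls for more robust follow-up studies.

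Most of this stands, and it limits the weight of the point. It does not remove it. Hedging a result does not change the quantity sought from effect modification to prognosis, and the general caveat leaves the aim as written.

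A reader might go further in three ways that the article does not support:
- *That a main objective of the study cannot be answered.* The subgroup wording is a secondary purpose of the questionnaire.
- *That the article itself shows that untreated course differs by time since adenotonsillectomy over the therapy period.* Section 1.2 describes recurrence at 12 months and severity at 12 to 72 months after surgery. It does not describe spontaneous recovery within 10 or 20 weeks. A role for age or weight through growth over so short a period is plausible at most, and obesity is excluded in the non-syndromic study.
- *That a false subgroup finding is likely, and is multiplied over five tests.* The SD differences are assumed, no between-subgroup test is specified, and the variables are listed as examples. The only alpha stated, 0.005, belongs to the sample size calculation; whether it would govern subgroup comparisons is unknown.

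That misleading claims would be published, or would steer treatment, is likewise conjecture.

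**Conclusion.** The point holds as a minor one about wording. Under the design in section 2.3, differential benefit of OMT is not identifiable; only association between baseline characteristics and total change is. This conclusion follows from the structure and needs none of the assumed values. It would fail only if untreated change were nil or equal across subgroups.

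The size of any spurious difference is unknown. The range of 12% to 51% at alpha 0.05 (2% to 19% at 0.005) for a 14/13 split is an illustration. It rests on an assumed 0.3 to 0.8 SD difference in untreated change, no difference in OMT effect, and a t test that the article does not specify. It is not an error rate of the planned analyses, and the overall pre-post comparisons are not altered by this point.

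**What to change.** In section 2.5, replace the aim of finding who benefits most with an exploratory, hypothesis-generating description of baseline characteristics associated with change over the therapy period. Add one sentence there, or beside the control-group caveat in the Discussion, saying that these associations cannot be read as differential benefit of OMT because untreated change may differ between subgroups. Report them as estimates with confidence intervals, not as responder subgroups picked out by significance.

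This needs no extra children, visits or measurements. The cost is a less ambitious claim. If the stronger aim is to be kept, an untreated reference is required, such as a waiting-list period, a repeated baseline, or a concurrent control with a test of interaction. That would be a change of design with its own burden, and the small secondary aim does not by itself call for it.

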### 2.6. Assessment Protocol

The effect of OMT in non-syndromic children (pretest–posttest study 1) and children with Down syndrome (pretest–posttest study 2) with OSA will be determined on (1) orofacial myofunctional, (2) sleep, and (3) Quality of Life (QoL) measures.

#### 2.6.1. Orofacial Myofunctional Assessment

Orofacial myofunctional outcomes will be evaluated during a perceptual and instrumental orofacial myofunctional assessment by 2 speech-language pathologists (SLPs) specialized in orofacial myofunctional disorders of Ghent University. These researchers will not be involved in the treatment and will be blinded for the study purposes.

#### 2.6.2. Oromyofunctional Postures, Mobility, and Functions

A perceptual orofacial myofunctional evaluation will be performed, using the Orofacial Myofunctional Evaluation with Scores (OMES) protocol, to evaluate posture (face, cheeks, tongue, lips, palate, maxilla/mandibula relation and mentalis muscle), mobility (lips, tongue, cheeks and jaw) and functions (breathing, deglutition and mastication) of the oropharyngeal structures [46]. Analysis of the OMES protocol is based on predefined ordinal rating scales and will be performed based on video recordings. Samples will be randomized and blindly evaluated by 2 specialized SLPs. The video recordings of the rater with the highest intra-rater reliability will be used for further analysis.

#### 2.6.3. Tongue and Lip Strength and Endurance

The IOWA Oral Performance Instrument (IOPI) (model 2.1; IOPI Medical LLC, Carnation, WA, USA) will be used to measure maximum lip and tongue strength and endurance following the instructions of Van Nuffelen et al. [47].

### 2.7. Sleep Assessment

#### 2.7.1. Screening for Pediatric Sleep Disorders

The Sleep Disturbance Scale for Children (SDSC) is a validated, parent-reported questionnaire to assess the presence of sleep disorders in children. Comprising 26 items on a 5-point Likert scale, the SDSC evaluates sleep disorders on six domains: disorders of initiating and maintaining sleep, sleep disordered breathing, disorders of arousal, sleep–wake transition disorders, disorders of excessive somnolence, and sleep hyperhidrosis [48,49]. Different types of sleep disorders can co-occur and symptoms can overlap among various pediatric sleep disorders. Therefore, it is important understand the child’s overall sleep health and identify potential co-occurring sleep disorders that may affect treatment outcomes.

#### 2.7.2. OSA Severity and Symptoms

All children will undergo a full-night laboratory polysomnography (PSG). The PSG will be performed and scored according to the standard criteria of the American Academy of Sleep Medicine by specialists from the Pediatric Sleep Center [46,47,50]. Electroencephalogram (EEG), chin electromyogram (EMG), and electrooculogram tracings will be used to determine sleep stage. In addition, PSG will provide data regarding respiratory events by measuring abdominal movements with strain gauges, oronasal airflow with an oronasal thermal sensor and nasal pressure transducer, and oxygen saturation with pulse oximetry. Snoring sounds will be detected by a snore microphone, and limb movements will be recorded using EMG [28,50]. PSG will objectively evaluate OSA severity (i.e., AHI, Arousal Index, Oxygen Desaturation Index, sleep efficiency) and OSA symptoms (i.e., snoring frequency). PSG results will be processed and interpreted by an expert at the Pediatric Sleep Center.

The Pediatric Sleep Questionnaire (PSQ) will be completed by the child’s parents to evaluate OSA symptoms. Twenty-two items within the following domains: snoring, observed apnea, daytime fatigue, and OSA-related behavioral disturbances will be scored on a dichotomous scale (present/absent). The variable obstructive Sleep-Related Breathing Disorder score (SRBD score) will be derived from the questionnaire by calculating the average of the non-missing items [51]. This questionnaire was proven to be reliable and valid with high sensitivity and specificity [52].

The Child Sleep Habits questionnaire (CSHQ) will be completed by the child’s parents to evaluate sleep disorders in children [53]. Thirty-three items within the following domains: bedtime resistance, sleep-onset delay, sleep duration, sleep anxiety, night wakening, parasomnias, sleep disordered breathing, and daytime sleepiness are rated on a 3-point scale. The CSHQ was proven to be reliable and valid [53].

#### 2.7.3. Quality of Life Assessment

Sleep-related quality of life evaluation will be performed using the 28-item parent-reported Child Health Questionnaire (CHQ). The CHQ is a valid and reliable tool to assess the impact of OSA on quality of life [54,55].

### 2.8. Intervention

#### 2.8.1. Oromyofunctional Therapy

All participants will receive an OMT program that consists of one individual session of 45 min per week for a period of 10 weeks and 10 min daily home practice. For children with Down syndrome, therapy duration is extended to 20 weeks, together with 10 min daily home practice [35]. The exercises are taught during the weekly sessions and practiced together with the child in a playful and guided manner. Subsequently, the child repeats the exercises daily at home according to the prescribed number of repetitions. Appendix A outlines which exercises are introduced in each week and subsequently practiced at home, both for non-syndromic children and children with Down syndrome, including the number of repetitions required for each exercise during home practice. Four therapeutic goals are selected based on literature and therapeutic experience to improve muscle resistance, balance the contraction of pharyngeal muscles, and correct abnormal functional and resting postures of the oropharyngeal structures in order to stabilize the upper airway during sleep [29,30,31,54,55,56]. The following therapy goals were established: Goal 1: Rehabilitation of nasal breathing; Goal 2: Stabilization of a closed mouth posture (competent lip seal) by correct position of jaw and lips; Goal 3: Stabilization of correct tongue posture, including differentiated tongue movement; Goal 4: Increasing strength and endurance of upper airway muscles. The specific exercises chosen to reach these goals were based on both evidence from the literature as well as insights from clinical experience [53,54,56,57,58]. Existing exercises were modified to ensure accessibility for young children and children with cognitive impairments. Adaptations included the incorporation of visual feedback components and enhancements to increase the exercises’ appeal and comprehensibility for the target population. An overview of all exercises selected and developed for each therapy goal is presented in Appendix A.

#### 2.8.2. Therapy Provider and Treatment Fidelity Checks

Therapy is provided by an SLP ([name]) with experience in the diagnosis and treatment of OMDs in children. All therapy will be provided by the same SLP to avoid therapist effects. Treatment fidelity checks will be performed by two SLPs blinded to the research purpose. These SLPs will review video recordings of randomly selected therapy sessions taking into account an equal distribution between the groups.

